## Abstract

**Background::**

Chronic non-specific low back pain (CNLBP) is a common complaint about medical care and carries a heavy social burden. The efficacy of Tuina (TN) or physiotherapy (PT) for CNLBP has been evaluated in previous systematic reviews. However, there is no high-quality evidence to support the efficacy of Tuina. Therefore, this study aims to conduct a large-scale, multicenter, high-quality clinical trial to provide evidence for Tuina to treat CNLBP.

**Methods::**

This is a multicenter, assessor-, and analyst-blinded, randomized controlled trial with 3 parallel arms: TN, PT, and TN combined with PT (Tuina combined with physiotherapy) group. Six hundred twelve eligible CNLBP patients will be randomly assigned to the groups in a 1:1:1 ratio in 3 centers. The TN intervention includes 9-step routine techniques, while the PT intervention includes a physiotherapy treatment plan based on a patient's symptoms. The interventions for both groups will last for 30 minutes and will be carried out for 6 sessions in 8 weeks. The primary outcome will be the visual analog scale pain score. And the secondary outcomes will include the Oswestry Disability Index, spinal range of motion, 36-item short-form health survey. Safety evaluation will be recorded during the whole study. All data in this randomized controlled trial will be analyzed by SAS 9.4.

**Discussion::**

The results of this trial will provide evidence to evaluate the efficacy of Tuina's value as a treatment for CNLBP.

**Trial registration::**

Chinese Clinical Trial Registry (ChiCTR2000040288, November 27, 2020).

## Introduction

1

Low back pain (LBP) is a common clinical symptom prompting patients to seek medical care. 80% of adults experience LBP during their lifetime.^[1]^ It is the leading cause of disability worldwide, with a global prevalence of 7.3% in 2016.^[2]^ Usually, most people recover with or without treatment, however, a relapse of the pain is common and 10% to 15% of LBP patients may develop chronic low back pain (CLBP).^[3]^ CLBP can be categorized into sciatica/nerve root pain syndrome, specific low back pain, and non-specific low back pain.^[^4^,^^5^^]^ The common causes of CLBP can include spinal injury, lumbar muscle strain, degenerative spinal intervertebral disc and vertebra joints, and kidney disease in women. 90% of CLBP patients do not have a clearly identifiable cause of pain, classified as chronic non-specific low back pain (CNLBP).^[^6^,^^7^^]^ CNLBP refers to pain and discomfort localized in the area between the costal margin and the inferior gluteal fold, not resulting from an identifiable or known specific pathology, with or without referred leg pain of >12 weeks’ duration.^[^8^,^^9^^]^ CNLBP's symptom onset, recovery, and clinical outcomes are influenced by biological, psychological, and social factors; therefore, its management is often complicated and multimodal.^[10]^

As the pathoanatomical cause of CNLBP remains an enigma, no specific evidence-based clinical practice method has been recommended for medical providers to manage CNLBP.^[^11^,^^12^^]^ According to the Consensus on the management of LBP,^[13]^ there is a wide variety of approaches recommended for CNLPB, such as patient education, self-management, physiotherapy, psychological therapy, medication, injection, ablation techniques, or surgery. Although these treatments have shown some efficacy, there is no conclusive evidence for their continued use in the mainstream medicine or sufficient knowledge of the extent of their side effects.^[12]^ Nonetheless, a multidisciplinary eclectic rehabilitation strategy is often recommended for patients with CNLBP.^[14]^ More and more people have turned their attention to complementary and alternative medicine (CAM) treatment.^[^15^,^^16^^]^ At present, Tuina therapy has been widely accepted as a CAM modality.^[17]^

Tuina (TN), also named “Tui Na,” literally means “pushing (and) grasping” and has been used in China for thousands of years. It is a non-pharmacological manual therapy in traditional Chinese medicine (TCM), which is mainly applied to the meridians or acupoints, which are pathways for the qi and blood of the human body, by manipulation of pushing, grasping, pressing, rubbing, etc. Over the years, TN has developed currently into one of the most popular TCM therapies with a wide range of techniques for various body locations.^[18]^ It is proposed to treat diseases by removing the obstruction in Meridian collaterals and relieving pain by reducing inflammation, separating tendon adhesions, improving circulation, and re-aligning minor joint disorders.^[19]^ The use of TN as a treatment intervention has also been studied for other forms of pain management, pediatric cerebral palsy disorders, neurological and musculoskeletal conditions, and rehabilitation.^[20]^ In recent years, many studies have emerged to evaluate the effectiveness of TN to manage LBP.^[^21^–^23^]^ A systematic review and meta-analysis^[23]^ assessed the efficacy of TN-focused integrative Chinese medical therapies on LBP inpatients, incorporating 20 randomized controlled trials (RCTs). This review found that TN might be practical (SMD: 1.17; 95% CI 0.75–1.60 on pain; SMD: 1.31; 95% CI 0.49–2.14 on functional status) for inpatients with LBP, although more high-quality RCTs with longer follow-up were required to raise the level of evidence for its use for LBP.

There are also many studies on the therapeutic effect of TN on patients with CNLBP.^[^21^,^^24^^–^28^]^ Still, most of these trials involve the combination of TN with other CAM therapies^[^21^,^^24^^,^^25^^,^^27^^]^ or were conducted on a small sample size with poor methodological quality. There is insufficient evidence for the effective treatment of CNLBP using TN. TN is still not included in guidelines for LBP treatment in most countries,^[29]^ especially those using mainly Western forms of medicine. Therefore, the purpose of the study is to evaluate the effectiveness and safety of TN in the management of CNLBP.

## Methods and analysis

2

### Study design

2.1

This is a prospective, multicenter, assessor-, and analyst-blinded RCT of TN for CNLBP. Six hundred twelve patients will be allocated to one of the 3 groups: TN, PT, or Tuina combined with physiotherapy (T&P).

The study design is illustrated in the flow chart in Fig. 1 and the study schedule is presented in Fig. 2. And this protocol follows the 2013 SPIRIT^[30]^ (Standard Protocol Items: Recommendations for Interventional Trials) Guideline.

**Figure 1 F1:**
[figure not shown]
Flow chart of the study. A total of 612 participants will be randomized to the 3 groups. The study period will consist of the baseline, end of 2-month intervention, 3 months post-intervention. FAHJNU = First Affiliated Hospital of Jinan University, MC = Mayo Clinic, SGH = Singapore General Hospital.

**Figure 2 F2:**
[figure not shown]
Schedule of the study. Each session lasts about 30 minutes, for 6 sessions, over a total of 8 weeks. ODI = Oswestry Disability Index, RCT = randomized controlled trial, ROM = range of motion will be recorded at these points of assessment, SF-36 = 36-item Short-Form Health Survey, VAS = visual analog.

### Ethics and registration

2.2

The study protocol has been approved by the Ethics Committee /Institutional Review Board of the First Affiliated Hospital of Jinan University (KY-2019–042), the Mayo Clinic (20–003549), and the Singapore General Hospital (CIRB 2020/2798). And the approved protocol version is 11.0, at October 2020. Any protocol amendments will be detailed in the trial registration. We will follow the International Conference Guideline for Good Clinical Practice to ensure that the data and the results are credible. Before starting the study, investigators will inform patients of relevant information, including this clinical trial's potential benefits and possible harms. All the information provided from patients, such as personal health information, would be kept confidential.

This trial is recruiting patients now. Participant recruitment started in December 2020 and is expected to end in December 2022. It is registered on November 27, 2020 with the Chinese Clinical Trial Registry, and the registration number is ChiCTR2000040288.

### Participants and recruitment

2.3

Eligible participants include patients diagnosed with CNLBP according to the Chinese Association for the Study of Pain (CASP) Consensus for the management of CNLBP (Inclusion 1, 2, 3).^[13]^ Patients presenting for the first time to either the Rehabilitation (Physiotherapy), General Internal Medicine Department, or Acupuncture Department in the hospital or clinic for low back pain for over 3 months, will be informed of this trial. If the patient expresses interest, a clinical trial communicator/research assistant will contact them to briefly introduce the trial and assess their suitability based on the study's inclusion and exclusion criteria.

### Inclusion criteria

2.4

Those who meet the following criteria are eligible to participate in the study:

(1)Pain and discomfort of unknown etiology between the costal margins and inferior gluteal folds with or without referred pain to the lower limbs, lasting for >12 weeks.(2)Has at least one symptom of spinal muscle weakness, stiffness, limited mobility, or reduced spinal coordination. The symptoms of pain are lessened or disappeared after bed rest, while pain symptoms are aggravated after bending over, sitting for a long time, or standing for a long time.(3)Physical examination showed increased muscle tension or a significant localized tenderness point (trigger point) in the painful area, with a negative straight-leg raising test and no signs of nerve root lesions.(4)Patients are older than 21 and younger than 75 years of both sexes.

### Exclusion criteria

2.5

Those who meet any of the below exclusion criteria shall be excluded from the study:

(1)Patients with LBP associated with nerve root dysfunction.(2)Patients with severe skin diseases (e.g., skin cancer, erysipelas, severe eczema, severe dermatitis, severe psoriasis, and severe hives lupus).(3)Serious spinal pathologies such as fractures, tumors, inflammatory, and infectious diseases.(4)History of spine surgery.(5)Serious cardiovascular or metabolic disorders, such as heart failure, severe osteoporosis.(6)Patients diagnosed with cognitive issues such as major depression, and moderate to severe dementia, and/or severe psychiatric diseases (such as schizophrenia, bipolar affective disorder, paranoid psychosis).(7)Women who are pregnant or of childbearing potential and are likely to become pregnant during the treatment phase but are not willing to use a reliable form of contraception will also be excluded. Reliable forms of contraception include oral contraception, diaphragm or condom (with spermicide), injections, intrauterine devices, surgical sterilization, and abstinence.

### Suspension criteria

2.6

Subjects may discontinue from the study after discussions with the clinicians for the following reasons:

(1)The subject has an adverse reaction to the intervention.(2)The subject's pain score decreased to 0.(3)The subject wishes to withdraw from the clinical study.(4)The subject wishes to attend other interventions, which may result in the study bias, such as attending chiropractic or other massage therapy or non-traditional spinal treatment.

Those who meet any of the above suspension criteria shall be suspended. However, all subjects’ responses will be recorded to determine the reasons for suspension from the study and the intention-to-treat analysis.

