### Outcome measurements

2.11

The primary outcome measure assesses the efficacy of massage therapy for the treatment of CNLBP: change in low back pain measured by the 100 mm VAS^[31]^ over the 2-month treatment. Secondary outcome measures included the Oswestry Disability Index^[32]^ (ODI), spinal range of motion^[33]^ (ROM), and the 36-item short-form health survey^[34]^ (SF-36). Fig. 2 demonstrates all measurements and measuring time points.

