### Safety evaluation

2.12

Since TN and PT are both non-invasive external treatments, the side effects are minor, but in the course of operation, if the technique is misused, there may be accidents such as muscle, bone, or joint damage of the spine or other parts of the body. Therefore, the response to an adverse event should strictly follow the standard operating requirements to prevent accidents.

Pre- and post-treatment of each treatment session, the researchers will review the patient's symptoms according to the following safety classification:

Level 1: Safe, without any adverse reactions and treatment can continue.Level 2: Relatively safe, with minor adverse reactions, treatment can be continued without any additional remedial treatment for the injury.Level 3: There are safety problems, moderate adverse reactions, and treatment can continue after treatment of the injury.Level 4: Suspension of participation in research due to adverse reactions.Adverse events such as changes in pain, syncope, vertigo, and lumbar function degradation, will be carefully recorded in the case report form.

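### Section 2.6 makes a pain score of 0 a reason to leave the study rather than to stop treatment, so exit depends on the primary outcome; its adverse-reaction criterion also conflicts with Section 2.12

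*Protocol article*

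**What the plan says.** Section 2.6 opens: "Subjects may discontinue from the study after discussions with the clinicians for the following reasons". The list that follows includes an adverse reaction (criterion 1, "The subject has an adverse reaction to the intervention", with no grade) and a "pain score decreased to 0" (criterion 2). It then states: "Those who meet any of the above suspension criteria shall be suspended". The next sentence is a safeguard: all subjects' "responses will be recorded to determine the reasons for suspension from the study and the intention-to-treat analysis".

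The primary outcome in Section 2.11 is "change in low back pain measured by the 100 mm VAS" over the 2-month treatment. Section 2.14 plans data at baseline, at the end of the intervention and 3 months later, and names no exception for suspended patients. Section 2.13 adds a telephone call about recurrence in week 20. Section 2.16 requires only a baseline evaluation of the primary outcome for the full analysis set, beyond the safety-set criteria. For missing data it looks at the reason, mentions an imputation approach and then names last observation carried forward (LOCF).

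Section 2.12 grades reactions. At Level 2 there are "minor adverse reactions, treatment can be continued without any additional remedial treatment for the injury". At Level 3 there are "moderate adverse reactions, and treatment can continue after treatment of the injury". Only Level 4 is suspension from the research.

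**The concern.** There are two separate problems.

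**Pain of 0.** A complete response is a reason to stop treatment. It is not a reason to stop observing the patient. Under Section 2.6 it is a reason to leave the study, so the chance of having an observed week-8 score may depend on the score itself, and more patients would leave from the arm with more complete responders. A single 0 is also a poor stand-in for week 8. Inclusion criterion 2 selects patients whose pain eases or disappears with bed rest and worsens with bending, sitting or standing, and the Introduction says that relapse is common. A patient with no week-8 VAS stays in the full analysis set and falls to LOCF. If the 0 is carried, any return of pain before week 8 is hidden, which favours the arm with more early zeros.

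**Adverse reactions.** If shall be suspended is taken at its word, a patient with a minor or moderate reaction must be suspended under 2.6(1) and may continue under 2.12. Three centres need one rule.

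**Working it through.** **1. Text side by side.**

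| Question | Section 2.6 | Elsewhere |
|---|---|---|
| Stop what? | The study | 2.12: treatment continues at Levels 2 and 3 |
| Optional or required? | *May*, then *shall* | 2.12: suspension only at Level 4 |
| Week-8 VAS after suspension? | Responses recorded for intention-to-treat; no visit or measure named | 2.14: end-of-treatment data planned in general; 2.13: week-20 call; Fig. 2 not shown |

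Under *may*, 2.6(1) and 2.12 can be reconciled. Under *shall*, they cannot both be followed for a Level 2 or Level 3 patient.

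**2. The plan's own figure.** Section 2.7 gives changes of 1.4 (0.8) for Tuina (TN), 1.9 (0.9) for the combination (T&P) and 1.65 (0.85) for physiotherapy (PT). A one-way ANOVA with three equal groups, common SD 0.85, alpha 0.05 and 80% power needs 57 per group (power 0.802). Then 57/0.85 = 67.06, rounded up to 68 per group, or 204 per centre. The sample size reproduces and is not in dispute. Pooled over three centres there are 3 × 68 = 204 per arm.

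**3. Size of the effect if week 8 is missing after a 0.** The documents give neither baseline VAS nor session-to-session variation, so this rests on assumptions: Section 2.7 changes read as cm; baseline normal, truncated to 0–10 cm, mean 5 or 6, SD 1 or 1.5; linear individual decline that matches the Section 2.7 means and SDs; noise SD 0.3 or 0.6 cm per score; scores rounded to 1 mm and floored at 0; six sessions (weeks 0 to 7.5), each scored before and after treatment; exit at the first 0 before week 8. Shift = (T&P − PT difference in improvement after replacing the week-8 value) − (true difference). One million simulated patients per arm; a rerun agreed closely. The true difference came out at 0.242–0.251 cm, so Section 2.7 is reproduced.

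| Scenario, mean baseline 5–6 cm | Exit, T&P | Exit, PT | Shift if 0 is carried |
|---|---|---|---|
| No dip after sessions | 0.1–4.6% | 0.0–3.2% | 0.000 to +0.004 cm |
| 1 cm dip just after each session | 0.5–11.5% | 0.3–9.0% | +0.002 to +0.017 cm |

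Without a dip, the most exits are 0.046 × 204 ≈ 9 and 0.032 × 204 ≈ 7 patients. The largest shift is 0.017/0.25 = 6.8% of the planned T&P − PT difference. The standard error of that contrast is √((0.9² + 0.85²)/204) = 0.087 cm, so the shift is at most 0.017/0.087 ≈ 20% of one standard error.

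**4. Two sensitivities.**
- *Lower baseline.* Section 2.4 sets no minimum pain score. At an assumed mean of 4 cm, exit is 6–14% (T&P) against 4–11% (PT) without a dip, and 19–28% against 14–24% with one. The shift from carrying 0 is then at most +0.03 cm.
- *True relapse.* The simulation has steady decline and no relapse. If those who exit have week-8 pain of r in both arms, the shift is (difference in exit share) × r. With the largest exits in the table, r = 0.5 to 2 cm gives (0.046 − 0.032) × r = 0.007 to 0.028 cm without a dip, and (0.115 − 0.090) × r = 0.013 to 0.05 cm with one.

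The shift is zero if exit and the week-8 scores of those who exit are equal across arms. TN was not simulated.

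**The case against.** The strongest reply is that the article does intend to keep these patients. The sentence on suspension is followed at once by one that records all subjects' responses for the intention-to-treat analysis, Section 2.14 plans end-of-treatment data without exception, and Section 2.13 telephones participants in week 20. Fig. 2 and approved protocol version 11.0 are not shown, and an article commonly leaves visit-level instructions to the full protocol. This stands. A reader might infer that week-8 scores of suspended patients will be lost; the documents do not support that. What remains is the stated rule itself: exit is from the study, it is triggered by the outcome, and it is worded both as optional and as required.

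A second reply is that the effect is negligible. At the assumed baselines and without relapse, that is nearly right. A reader might infer a much larger bias by supposing that LOCF returns to baseline and turns a complete response into no change. With mean baseline 5 cm and the 1 cm dip, this would shift T&P − PT by up to −0.077 cm, or 0.077/0.25 = 31%. The documents do not support it: criterion 2 can apply only once a 0 has been observed, nothing says that only scheduled visits count, and both the dip and the VAS at each session are assumptions.

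A third reply is that 2.6(1) names a reason and 2.12 says at what level it applies. That reading is sensible, but *shall* together with *any* criterion works against it.

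**Conclusion.** The point holds as a fault in a stated rule, of moderate weight. Section 2.6 makes exit from the study depend on the primary outcome, and read with *shall* its adverse-reaction criterion contradicts Section 2.12. The second part needs no numbers.

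Whether week-8 VAS values would be lost is open. If they were, the likeliest result is a carried 0 and a bias on T&P − PT of about 0.00–0.02 cm at assumed mean baselines of 5–6 cm. Lower baseline pain or true relapse before week 8 would make it larger. These figures show an order of magnitude under assumptions; they are not an estimate from the documents. The case for change rests on how easily the rule is corrected, not on a large expected bias.

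**What to change.** Amend Section 2.6 as follows:

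- Make pain of 0 and the other listed reasons grounds to stop treatment only. Withdrawn consent is the one exception.
- State that all randomised patients are assessed at the scheduled week-8 and week-20 points, and that the observed values are analysed.
- Limit 2.6(1) to Level 4 of Section 2.12, in wording set by the clinical team.
- Replace *may* and *shall* with one rule.

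If the full protocol or Fig. 2 already secures the week-8 VAS after suspension, the sponsor need only confirm that part. The cost is amendment wording and a few more assessments at visits already scheduled. The sample size does not change.

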### Sample size calculation

2.7

This is a randomized controlled trial with 3 parallel arms. The test groups are the TN and T&P groups; the control group is the PT group. The visual analogue scale (VAS) score is the primary outcome. We use ANOVA to calculate the sample size. According to the previous report,^[24]^ the mean (standard deviation) difference of the VAS score of pre- and post-treatment in the TN group, T&P group, and PT group is 1.4 (0.8), 1.9 (0.9), and 1.65 (0.85), respectively. Assuming *α* = 0.05 (2-sided), *β* = 0.80, 171 subjects (57 subjects per group) are needed to achieve an 80% probability of detecting difference (PASS software, Ver. 11, NCSS, LLC. Kaysville, Utah; www.ncss.com). When considering a potential dropout risk of 15%, a total of 204 subjects (68 subjects per group) will be required as a sample size for statistically significant results at each center.

Stratified by 3 centers, the combined sample size is 612 for a meta-analysis.

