### Statistical analyses

2.16

The analysis set will consist of a full analysis set (FAS), a per-protocol set, and a safety set. The safety set will include randomly assigned participants and receive at least one intervention treatment. The FAS will consist of data indicating that the treatment was as close to the intention to treat as possible. In addition to meeting the safety set criteria, the participants must have been evaluated for the primary outcome at least once at the baseline. The FAS will be used in the primary analysis. For missing data, we will analyze the underlying reason and use an imputation adjustment approach, and the last observation carried forward analysis will be used to handle the missing data. After the primary analysis, a sensitivity analysis will be performed by comparing the results from the per-protocol analysis and the intention to treat analysis to evaluate the impact of missing data on the trial results. Besides, subgroup analyses by the center will be done.

(1)Statistical analysis methodFor all of the analyses, SAS version 9.4 was used. The confidence interval will be established at 95%, and the significance level at 0.05.Continuous variables were analyzed with an ANOVA test if normally distributed (results are presented as means ± SD) or Kruskal-Wallis H test if not normally distributed (presented as median with interquartile range). Multiple comparisons were addressed using the Tukey post hoc test (for ANOVA), and Bonferroni correction (for Kruskal–Wallis). The classification count data is checked by the chi-square test. This study used a one-sided test. When *P* < .05, the difference was considered statistically significant.(2)Statistical analysis contenta.Baseline evaluation: Social demographic characteristics, baseline severity analysis.b.Efficacy evaluation: We use the low back pain VAS score sheet, spinal ROM sheet, ODI scale, SF-36 scale, and the number of treatment sessions.c.Safety evaluation: Evaluation was made by the incidence of adverse events or recurrence of pain, or further injury from accidents during the follow-up period, and the level of safety.d.Compliance evaluation: Evaluation was carried out using the compliance rate.

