## Discussion

3

CNLBP is a significant health issue worldwide. Given its prevalence, the need to assess practical approaches for low back disorders is of prime importance. TN is one of the essential parts of TCM and has contributed to people's health in China for thousands of years. A considerable body of scientific evidence supports such therapies for CNLBP treatment, but their efficacy has not been established.^[35]^ Therefore, it is essential to provide robust evidence about the effectiveness of TN for CNLBP.

The present trial is a comparative effectiveness study of TN (intervention) and PT (control) for pain relief and functional recovery in patients with CNLBP. We evaluated 3 aspects of CNLBP: pain, physical function, and quality of life. The VAS will be used as the primary outcome. The secondary outcomes are the ODI, which measures dysfunction and includes 10 questions on daily activities; the ROM, which evaluates functional limitations in everyday life; and the SF-36, which measures changes in health-related quality of life.

According to the theory of TCM,^[35]^ good physical health depends on qi and blood circulation. The common causes of pain are stagnation of qi and stasis of blood. Moreover, other pathogenic factors such as phlegm and dampness can be identified as causative factors in a blockage. TN can relieve pain by promoting qi and blood's local and systemic circulation by removing pathogenic factors. Studies have shown that TN may alleviate CNLBP by reducing inflammation and repairing damaged mitochondria in the skeletal muscle.^[36]^

The results of this RCT will contribute to the clinical practice of TN for CNLBP. And the results will be presented in an open-access peer-reviewed journal and an academic conference.

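### The 80% power at 57 per group belongs to the omnibus three-group F test; each test arm against the PT control has 22–34% power per centre and 64–84% pooled (two-sided 5%)

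*Protocol article*

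**What the plan says.** Section 2.7 of the protocol article (Sample size calculation) gives the arms their roles: "The test groups are the TN and T&P groups; the control group is the PT group". It names the sizing method: "We use ANOVA to calculate the sample size". The assumed mean (SD) VAS change "in the TN group, T&P group, and PT group is 1.4 (0.8), 1.9 (0.9), and 1.65 (0.85), respectively". From these it concludes that "171 subjects (57 subjects per group) are needed to achieve an 80% probability of detecting difference".

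A 15% dropout allowance takes this to 68 per group and 204 per centre, which the section presents as the number each centre needs for its own results to reach significance. Three centres give 612 for a combined analysis.

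Section 2.16 (Statistical analyses) plans an ANOVA for normally distributed continuous outcomes and adds: "Multiple comparisons were addressed using the Tukey post hoc test (for ANOVA"). It makes the full analysis set (FAS) primary, with last observation carried forward (LOCF), and lists centre under subgroup analyses. It also says that tests are one-sided, whereas section 2.7 sets a two-sided 0.05.

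The Discussion describes the purpose: "The present trial is a comparative effectiveness study of TN (intervention) and PT (control) for pain relief" and functional recovery.

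No power is given for any comparison of a test arm with PT, per centre or pooled.

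**The concern.** The 80% has no contrast attached to it. Because PT is called the control and the Discussion frames the trial as TN against PT, a reader will take the 80% to cover those comparisons. It does not. A three-group F test can be significant because T&P differs from TN, which says nothing about either arm against the control.

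On the plan's own assumptions, the most likely result of a comparison with PT at a single centre is non-significance. If readers believe that comparison had 80% power, they may take a null result for TN versus PT as evidence that the two are alike. The assumed means add to this risk: TN is expected to improve by 1.4 and PT by 1.65, so the planning scenario has TN doing worse than the control.

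**Working it through.** **Inputs.** All are from sections 2.7 and 2.16: means TN 1.4, T&P 1.9, PT 1.65; SDs 0.8, 0.9, 0.85, taken as a common 0.85; alpha 0.05 two-sided; 57 evaluable per group per centre; 15% dropout; three centres; Tukey for pairwise comparisons.

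**1. Reproduce the plan's figure.** For the omnibus F test, λ = n·Σ(μᵢ − μ̄)²/SD².
- The grand mean is 1.65 and Σ(μᵢ − μ̄)² = 0.25² + 0.25² + 0 = 0.125.
- At n = 57, λ = 57 × 0.125/0.7225 = 9.86. With 2 and 168 degrees of freedom the critical F is 3.05 and power is 80.2%.
- At n = 56, power is 79.5%. So 57 is the smallest n that reaches 80%.
- 57/(1 − 0.15) = 67.1, rounded up to 68; 3 × 68 = 204; 3 × 204 = 612.

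Every stated number reproduces as an omnibus calculation.

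**2. Pairwise differences in the same inputs.**
- T&P − TN = 0.50 (test arm against test arm)
- T&P − PT = +0.25
- TN − PT = −0.25

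The largest gap does not involve the control. At 57 per group it has 88% power unadjusted and 78% with Tukey.

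**3. Power against PT.** The noncentrality is δ = 0.25/(0.85·√(2/n)). Unadjusted power uses the two-sample t critical value. Tukey power uses the studentized-range critical value for three groups divided by √2.

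| n per arm | Meaning | δ | Unadjusted, two-sided 5% | Tukey | Unadjusted, one-sided 5%* |
|---|---|---|---|---|---|
| 57 | one centre, evaluable | 1.57 | 34% | 22% | 47% |
| 171 (3 × 57) | pooled, evaluable | 2.72 | 77% | 64% | 86% |
| 204 (3 × 68) | pooled, all randomised | 2.97 | 84% | 73% | 91% |

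*For a 0.25 advantage in the tested direction, which is the assumed case for T&P versus PT.

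At n = 57 the critical values are 1.98 (unadjusted) and 2.36 (Tukey), both above δ = 1.57, so power is below one half. For 80% power on a 0.25 difference, the smallest n is 183 per arm unadjusted or 236 with Tukey.

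**4. Sensitivity to the SDs.** With arm-specific SDs (the root mean square of the two arms compared), unadjusted/Tukey power is:
- TN versus PT: 36%/23% at 57 and 80%/67% at 171
- T&P versus PT: 33%/20% at 57 and 75%/61% at 171

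The picture does not change.

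**5. Direction.** TN − PT is negative in the planning scenario. The two-sided power for TN versus PT is therefore power to find TN worse. A one-sided test of TN better than PT would have power of about 0.07% at 57 per arm.

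**The case against.** The strongest reply is that nothing is miscalculated. The section names ANOVA, the analysis section plans ANOVA, and 57 is exactly right for that test. This stands. A reader might infer that the sample size is arithmetically wrong, or that the 80% should be deleted; the documents support neither. The 80% is true of the F test and needs only to be labelled.

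A second reply is that single-centre figures show the trial at its worst, since 612 patients are to be combined and centre is a subgroup factor. This also largely stands: 22–34% is not the power of the trial. The per-centre figure still matters, because section 2.7 itself ties its 204 to significance at each centre. The pooled figure depends on who is analysed. The FAS requires only one treatment and a baseline VAS, and LOCF keeps later dropouts in, so up to 204 per arm may count. Power is then 84% unadjusted, above 80%, but 73% with the planned Tukey.

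Third, section 2.16 specifies one-sided tests, under which the unadjusted pooled figures are 86% and 91%. That conflicts with section 2.7 and must be settled, but even so one centre reaches only 47%.

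Fourth, a reader might infer that the plan sets out to prove TN superior and is bound to fail, or that a non-inferiority margin is missing. The documents state neither a superiority hypothesis nor an equivalence claim; they speak of comparative effectiveness. A margin or a ranked testing order may be in an analysis plan that is not shown. Nor is Tukey an error: it controls the error rate over all pairs, and preferring Dunnett or a fixed sequence is a choice.

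**Conclusion.** The point holds in a limited form. The 80% at 57 per group is correct for the omnibus F test but does not carry over to either comparison with PT, the control that the plan itself names. At two-sided 5%, power against PT is 22% (Tukey) to 34% (unadjusted) at one centre. Pooled, it is 64% to 77% with 171 evaluable per arm, or 73% to 84% with all 204 randomised.

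The shortfall is severe per centre. In the pooled analysis it is moderate and depends on the multiplicity method, the number analysed and the sidedness.

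These figures assume the plan's means, a common SD of 0.85, equal arms and no gain from baseline adjustment. The 204 case also assumes that LOCF leaves the difference and SD unchanged. Separately, the planning means cannot support an expectation that TN beats PT: on those means, a significant TN-versus-PT result would most likely show TN worse.

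**What to change.** In section 2.7:
- State that the 80% at 57 per group refers to the omnibus three-group F test.
- Remove the implication that each centre is powered for significant results against PT.
- Name the contrast or contrasts against PT as the comparisons of interest in the pooled, centre-stratified analysis, and give their power under the planned Tukey procedure: about 64–73% (77–84% unadjusted) at two-sided 5%, for 171 to 204 analysed per arm.

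In section 2.16:
- Reconcile the one-sided rule with the two-sided alpha of section 2.7, and quote power for the rule that is kept.
- Say that TN versus PT will be reported as an estimate with a 95% CI, and that non-significance will not be read as equivalence.

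Replacing Tukey with Dunnett or a fixed sequence is optional.

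The cost is wording in two sections and a less favourable stated power. No additional patients are needed.
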